#### Participant Recruitment and Management

We plan to recruit a total of 400 study participants, comprising 100 individuals formally diagnosed with ADHD, another 100 diagnosed with ASD, a further 100 diagnosed with both ASD and ADHD, and 100 individuals evaluated and confirmed to not have any socially related psychiatric conditions. Our inclusion criteria are as follows: (1) adolescents aged between 14 and 18 (inclusive) years and (2) formally evaluated for ADHD and ASD by a licensed clinician with available documentation. The selection of the final 400 participants that comprise our core data set will be based on the personal information that participants are asked to disclose. Such metadata will be used to ensure a data set that is balanced with respect to race, ethnicity, and gender. The number of participants is based on testing the ability of our system to discriminate between groups of participants. As these groups are balanced, we set the prevalence for binary classification between each condition to 50%. Following a CI of 95%, an estimated theta of 95% [42,48,49], and a width of 15%, the sample size to compute the area under the receiver operating characteristic curve (AUROC) should be 37 [54]. Considering that we have 400 participants, with 100 participants per group, this enables us to follow a common 60:20:20 (train, validation and test ratio respectively) randomized split on the data. That is, we have a sample size (test set) of 40 participants to verify the system’s ability to discriminate between the neurotypical participants and the participants who were diagnosed with either ASD, ADHD, or comorbid ASD and ADHD.

Although formal and well-established methods to perform power calculations for ML analyses have yet to be established, most digital diagnostics studies for conditions such as ASD include <100 participants per class in binary classification [47]. We aim to maintain a similar sample size per diagnostic category. The digital social experiences will be delivered to study participants for 15 minutes each day for a 3-week duration, with a single game out of the 7 possible delivered each day. At least 3 distinct 15-minute sessions will be collected per game for each participant, allowing for comparisons across days for analysis of within-peer consistency.

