The other potential pitfalls are compliance and tardiness. We will run automated computer vision checks in real time to ensure participant compliance with camera calibration requirements. Another script will send automated text messages and email reminders to late participants, assigning them to makeup sessions. If these mitigation steps fail or if recruitment is unsuccessful and there are <100 participants with valid data per diagnostic category, the study can still be successful with as few as 20 participants per class, as ML studies with approximately 20 participants per diagnostic category have frequently been published in the field [47].

There are also limitations associated with crowdsourcing based on the expertise of the crowd workers or their temporal availability. Although this never occurred during preliminary data collection, a potential pitfall is that some questions may have no workers who consistently rate them in accordance with clinicians. If this occurs, then that question will be removed from any further components of the study (ie, removed as a feature for the diagnostic classifier).

In crowdsourcing, scaling the number of workers does not correlate with the time spent on recruitment. However, to ensure high-quality annotations, we do anticipate spending a considerable amount of time recruiting crowd workers. As mentioned previously, we plan a crowd worker profiling phase based on 20 tasks and data collected through pilot studies with our data-gathering platform. By periodically posing a gold-annotated question and providing a monetary bonus for correctly answering such questions, we incentivize workers to provide high-quality answers. On the basis of our prior studies, we expect that the level of compensation will lead to a worker retention rate of >90%. Furthermore, to account for the loss of workers, we will recruit 3 times more crowd workers than is minimally required for the study. With regard to the number of crowd workers required, we follow the study by Roitero et al [70]. As such, the recommended number of workers will be estimated based on a small amount of data collected during our pilot studies.

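### The 20-per-class fallback does not meet the protocol's own AUROC precision rule: a single 20% test set leaves 8 or 16 test participants against the stated 37

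*Protocol article*

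**What the plan says.** Under Participant Recruitment and Management, the protocol article bases its size on the precision of the AUROC. For balanced groups, "we set the prevalence for binary classification between each condition to 50" per cent. Then: "Following a CI of 95%, an estimated theta of 95% [42,48,49], and a width of 15" per cent, "the sample size to compute the area under the receiver operating characteristic curve (AUROC) should be 37". The planned 100 per group is linked to this figure through a "60:20:20 (train, validation and test ratio respectively) randomized split on the data", from which "we have a sample size (test set) of 40 participants to verify the system’s ability to discriminate". The same section adds that power methods for machine learning are not well established and that published studies in the field usually have fewer than 100 per class.

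Under Limitations, the article considers what happens if valid data fall below 100 per category. It says that "the study can still be successful with as few as 20 participants per class", and the reason given is "as ML studies with approximately 20 participants per diagnostic category have frequently been published in the field [47". The 37, the interval width and the split are not mentioned there.

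**The concern.** The sizing argument and the fallback use different standards. The first asks how precisely discrimination can be estimated in unseen participants. The second asks whether studies of that size have been published. A study cut from 100 to 20 per class loses four fifths of its test cases, and the fallback does not say what that does to the interval that justified the sample size.

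This matters because Limitations names recruiting and retaining 400 participants as the primary challenge, so the fallback may be used. A reader of the final report could then take an AUROC from a very small test set as having the planned precision. Limitations does warn that smaller data sets can bring overfitting, noisy outliers or sample bias, but it says nothing about loss of precision.

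**Working it through.** **Inputs** (Participant Recruitment and Management, unless noted): 95% confidence; AUROC A = 0.95; width 0.15; prevalence 50%; required number 37; test share 20%; fallback 20 per class (Limitations). A = 0.80 is my assumption for a less favourable case. For comparison, Table 3 gives 0.815 for the audio model.

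**Formula.** Hanley-McNeil variance:

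SE² = [A(1−A) + (n₁−1)(Q₁−A²) + (n₂−1)(Q₂−A²)] / (n₁n₂), with Q₁ = A/(2−A), Q₂ = 2A²/(1+A), and width = 2 × 1.96 × SE.

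At A = 0.95: A(1−A) = 0.0475, Q₁−A² = 0.00226, Q₂−A² = 0.02314; the last two sum to 0.02540.
At A = 0.80: A(1−A) = 0.16, and the two differences sum to 0.02667 + 0.07111 = 0.09778.

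**Step 1: the plan's own figure.** With 18.5 v 18.5, SE² = (0.0475 + 17.5 × 0.02540)/342.25 = 0.001438, so SE = 0.0379 and the width is 0.149. Solving for a width of 0.15 gives N = 36.36, rounded up to 37. The stated 37 is therefore the total over both groups, for a full width of 0.15. Reading 15% as a half-width would give 11. The 40 in the test set is 20% of 100 + 100.

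**Step 2: the same construction at 20 per class.** 20 × 0.20 = 4 test participants per class.
- Two-group contrast: 4 + 4 = 8, or 22% of 37.
- ASD or ADHD classifier (Multicondition Diagnostics With Adaptive Input Querying, Description): each has two of the four groups on either side, so 8 + 8 = 16, or 43% of 37.
- The whole four-class test set is also only 16.

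**Step 3: widths.**

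| Test cases | SE² at 0.95 | Width at 0.95 | Width at 0.80 |
|---|---|---|---|
| 4 v 4 | (0.0475 + 3 × 0.02540)/16 = 0.00773 | 0.345 | 0.660 |
| 8 v 8 | (0.0475 + 7 × 0.02540)/64 = 0.00352 | 0.233 | 0.450 |
| 20 v 20 | (0.0475 + 19 × 0.02540)/400 = 0.00133 | 0.143 | 0.278 |

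The 0.80 column uses the same formula; for 8 v 8, SE² = (0.16 + 7 × 0.09778)/64 = 0.01319 and the width is 0.450. The 20 v 20 row is the case where all participants of a two-group contrast contribute one out-of-fold prediction each.

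The normal approximation is poor in the smallest rows. At 4 v 4 the upper limit passes 1, and a logit-scale interval would be wider (about 0.34 to 0.999). The shortfall in numbers, 8 or 16 against 37, does not depend on the approximation.

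**Step 4: number per class that supplies 37 from a 20% test set.**
- Two-group contrast: 37/2/0.20 = 92.5, about 93 per class.
- Pooled ASD or ADHD classifier: 37/4/0.20 = 46.25, about 47 per class.

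**The case against.** The strongest defence is that the diagnostic Evaluation section does not use one fixed test set. It derives performance and intervals by Monte Carlo cross-validation, so over many random splits nearly every participant is tested out of sample. Twenty per class then offers 40 distinct participants per two-group contrast, which exceeds 37, and the nominal width of 0.143 is inside 0.15. This stands in part, and it makes the failure conditional. However, the sizing section ties its 37 to a single test set, repeated splits reuse the same people and add no independent cases, and the 0.143 requires an AUROC of 0.95. The Results section itself expects the earlier autism-only performance to fall once ADHD is added. At 0.80 the width is 0.278 even with all 40.

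A second defence is that precision is not the only basis for the sample size, since the sizing section also appeals to typical published sizes. That is true, but such precedent does not supply the precision that the same section sets out to achieve.

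A reader might also infer that a study of 20 per class could not estimate any of its metrics and would still be declared a success. The document does not support that. Valid-frame compliance, participation, worker latency, interrater reliability, completion and deviation by privacy condition do not depend on a per-class test set. AUROC can still be computed, only imprecisely. The fallback is a contingency remark under Limitations and defines no success criterion.

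Nor is 93 per class a universal minimum. It applies to two-group contrasts; for the pooled classifiers the figure is about 47.

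**Conclusion.** The point holds as an inconsistency between two statements in the protocol article; the 37 itself is correctly calculated. Under the single 20% test set used for sizing, 20 per class gives 8 test participants per two-group contrast (width about 0.345, or 2.3 times the target) or 16 for the pooled ASD or ADHD classifiers (about 0.23, or 1.6 times the target). Every single-split reading falls short of 37. The precision rule is nominally met only if each participant supplies one out-of-fold prediction and the AUROC is as high as 0.95, taking the two-group contrast for which the article sizes the study.

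These results assume equal group sizes, the Hanley-McNeil variance with a normal-theory interval (which reproduces the plan's figure), and the 60:20:20 split. The Evaluation section's 300/50/50 split has a smaller test share (12.5%) and would leave 20 × 0.125 = 2.5 per class. That conflict between splits is a separate matter.

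**What to change.** In Limitations, replace the statement that 20 per class can still succeed with three statements:

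- With a single 20% test set, the planned precision (width 0.15 at AUROC 0.95) needs about 93 valid participants per class for a two-group contrast, or about 47 per class for the pooled ASD and ADHD classifiers.
- Below those numbers, discrimination will be evaluated from each participant's out-of-fold prediction. Confidence intervals will treat participants, not repeated splits, as the independent units, and the achieved width will be reported.
- At about 20 per class, results on diagnostic discrimination will be described as feasibility only. Compliance, participation and crowdsourcing metrics can still be reported as planned.

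The cost is a wording change and a less favourable fallback statement. Out-of-fold evaluation is close to the cross-validation already planned. No additional participants or data collection are required.

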### Conclusions

Given the complex nature of neuropsychiatric conditions, ML models can greatly reduce time to diagnosis, for example, by identifying salient information in support of establishing a diagnosis through a low-cost and remote data collection approach. Multimodal data with human-in-the-loop crowdsourcing may improve not only digital diagnostics but also our understanding of the complexity of the conditions. The crowd workers’ annotation can also provide data for other computer vision tasks, serving as a promising tool for genetic association, psychological, and kinematic studies.

## Abbreviations

ADHD: attention-deficit/hyperactivity disorder
ASD: autism spectrum disorder
AUROC: area under the receiver operating characteristic curve
AWS: Amazon Web Services
DL: deep learning
DSM-5: Diagnostic and Statistical Manual of Mental Disorders, Fifth Edition
IRB: institutional review board
ML: machine learning
